### Intervention

#### Exercise Intervention

Based on cardiopulmonary fitness and one repetition maximum, an individualized exercise training (combined aerobic and resistance exercises, three sessions per week) regimen will be developed. Each practice session will take 80 minutes, including 10 minutes of warm-up, 15 minutes of aerobic exercise, 10 minutes of resistance training, 10 minutes of rest, 15 minutes of aerobic exercise, 10 minutes of resistance training, and 10 minutes of relaxation. Aerobic and resistance exercises will include training with magnetic exercise bikes (HG-HRUB150T) and chest press/rowing (KY-701), abdominal and back muscle training (KY-705), and leg kick and hook (KY-703) machines (Nanjing Kuanyue Health Technology Co., Ltd, Nanjing, China). All aerobic and resistance training data will be recorded by an intelligent detection software system (Nanjing Kuanyue Health Technology Co., Ltd, Nanjing, China). The exercise training will be progressive and variable. Aerobic exercise programs will be divided into four training cycles (four weeks per cycle) and resistance exercise programs will be divided into three cycles. The differences in the training cycles will primarily be reflected in terms of the intensity and load. Details of exercise intervention are shown in **Table 3**.

**Table 3 T3:** Protocol of exercise intervention.

Phase	Week	Intensity	Load
Aerobic Exercise			
I	1 – 4 weeks	40% VO_2max_	Males: 35 W; Females: 25 W
II	5 – 8 weeks	50% VO_2max_	Males: 40 W; Females: 30 W
III	9 – 12 weeks	60% VO_2max_	Males: 45 W; Females: 35 W
IV	13 – 16 weeks	70% VO_2max_	Males: 50 W; Females: 40 W
**Resistance Exercise**			
I	1 – 6 weeks	50% 1RM	1-2 weeks: 8 times/muscle group * 2 group
			3-4 weeks: 10 times/muscle group * 2 group
			5-6 weeks: 12 times/muscle group * 2 group
II	7 – 12 weeks	60% 1RM	7-8 weeks: 8 times/muscle group * 2 group
			9-10 weeks: 10 times/muscle group * 2 group
			11-12 weeks: 12 times/muscle group * 2 group
III	13 – 16 weeks	65% 1RM	13-14 weeks: 8 times/muscle group * 2 group
			15-16 weeks: 10 times/muscle group * 2 group

Exercise intensity will be monitored and instructed using Rating of Perceived Exertion, with scope definition of 12 - 16. The intensity of exercise can be adjusted according to the weight and actual condition of participants. 1RM, 1 repetition maximum; VO_2max_, maximum oxygen uptake.

Participants in the exercise group will take part in exercise training at the Shanghai Jiao Tong University Affiliated Sixth People’s Hospital under the guidance of professional coaches. The duration and intensity of each exercise session will be recorded, and the coach will make personalized adjustments to the exercise intensity of each participant. The blood pressure, heart rate, and finger-stick blood glucose of participants will be recorded before and after the exercise session.

#### Diet Intervention

Diet intervention will be administered during the study period. The purpose of diet administration is to control the dietary intake of each participant and reduce the confounding effect of different dietary habits. The ideal body weight (kg) of an individual is equal to the height (cm) minus 105, and the recommended daily energy intake (kcal) is equal to the ideal body weight multiplied by 25 (kcal/kg). During the study, all participants will prepare and consume food based on a recommended diet chart, which will be prepared by a nutritionist according to the Dietary Guidelines for Chinese Residents (25) and Dietary Guidelines for Type 2 diabetes in China (26). To increase the dietary compliance, participants will be asked to take photos of each meal and record the type and volume of food that they consume on the Boohee Nutrition Mini Program (Shanghai Mint Health Technology Co., Ltd, Shanghai, China). Based on these records, the Boohee Nutrition Mini Program will automatically calculate and analyze the total energy intake, as well as protein, carbohydrate, fat, and other nutrient intake. Investigators will assess the dietary record on a weekly basis to assess adherence to the dietary regimens, and upload the dietary record to the data repository for further analysis.

### Study Outcomes

#### Primary Outcomes

Change in body fat mass measured by bioelectrical impedance analysis (DBA-210, software version 3.5, Donghuayuan Medical, Jilin, China).

#### Secondary Outcomes

Secondary outcomes include change rate of body fat mass, and changes in lean mass and percentage, anthropometric indicators (body weight, body mass index, and waist, hip, and thigh circumference), clinical biochemical indicators (HbA1c, insulin sensitivity, liver enzyme, renal function, blood lipid, blood glucose, serum insulin and C peptide), brain health (appetite, mood, and cognitive function), immunologic function, metagenomics, metabolomics, energy expenditure, cardiopulmonary fitness (maximum oxygen uptake, maximum oxygen uptake/predicted oxygen uptake), exercise-related indicators (physical activity, grip, flexibility, lower limb muscle endurance and strength, static and dynamic balance function, and muscle oxygen), fatty liver, cytokines (fibroblast growth factor [FGF] 21, FGF19, adiponectin, fatty acid-binding protein 4, and lipocalin 2), vascular endothelial function, autonomic nervous function, and glucose fluctuation.

### Data Management and Monitoring

The paper case report form for each participant will be filled by trained researchers. It will be used to collect information and will be kept strictly confidential for research purposes. Researchers will keep files intact, stored in a fixed place and locked at the Department of Endocrinology and Metabolism, Shanghai Jiao Tong University Affiliated Sixth People’s Hospital. All data will be scrutinized and double-entered by researchers. After the database is established and confirmed *via* blind audit, it will be locked and will not be changeable.

This study will be monitored by an independent Data Monitoring Committee comprising of specialists who are independent of this trial. Serious adverse events will be reported immediately to Data Monitoring Committee, principal investigator, and the Ethics Committee of the Shanghai Sixth People’s Hospital. The Data Monitoring Committee will audit the trial processes and data, and be responsible for discontinuing the trial.

### Sample Size Estimation

We will conduct an exercise intervention in two groups. The reduction in body fat mass will be the primary outcome. According to previous studies (27), the calculated sample size is 40 for each group to detect a 1.2 kg difference in body fat mass between two groups, with a significance level of 0.05 (α), statistic power of 80% (1-β), and standard deviation of 1.9 kg. Assuming a 20% loss to follow-up, a sample size of 50 will be required per group. Therefore, a total of 100 patients will be recruited.

### Statistical Analysis

Both the intention-to-treat and full analysis set analyses will be performed to examine effectiveness of exercise intervention on type 2 diabetes patients with abdominal obesity and low thigh circumference. Statistical analyses will be performed using SPSS 25.0 software (SPSS, Inc, Chicago, IL). Multiple imputations will be used to process missing values in the data. Data will be expressed as mean ± standard deviation, median (interquartile range) and percentage appropriately. Kolmogorov-Smirnov test will be used to determine the normal distribution of data. All statistical tests will be two-tailed, with a 0.05 significance level.

Baseline characteristics will be compared between groups by Student’s unpaired t-test for normal distributed data, Mann-Whitney test for non-normal distributed data, and Chi-squared test for categorical data, respectively. Comparisons between baseline and different time points (4, 8, 12, and 16-week follow-ups) in each group will be performed using paired t-test for normal distributed data and Wilcoxon signed-rank test for non-normal distributed data. Changes in clinical and multi-omics data before and after the intervention will be compared between groups using analysis of covariance, with baseline variable levels as covariates. Mixed-effect models will be performed to evaluate the effect of exercise intervention on clinical indicators. Additionally, multiple linear regression will be performed for sensitivity analysis of the main clinical variables, adjusting for age, sex, duration of diabetes, and diet. The composition of the gut microbiota will be analyzed from the metagenomic sequencing data using MetaPhlAn calculating software. Differences in the abundance of microbiota species before and after the intervention will be compared using Wilcoxon test. Differences in the abundance of microbiota between groups will be compared using Mann-Whitney test. Correlation between abundance of microbiota, metabolite levels, and clinical indicators will be analyzed using Spearman correlation and Partial correlation analysis.

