**Discussion:**

This study will evaluate the effect of a 16-week combined aerobic and resistance exercise regimen on patients with diabetes. The results will provide a comprehensive evaluation of the physiological effects of exercise, and reveal the role of the microbiota-gut-brain axis in exercise-induced metabolic benefits to diabetes.

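### The blanket 0.05 level covers the species, multi-omics and correlation screens with no stated false discovery control

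*Protocol article*

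**What the plan says.** The Statistical Analysis section of the protocol article sets the level for every test in one sentence: "All statistical tests will be two-tailed, with a 0.05 significance level". It makes no exception and mentions no adjustment. The high-dimensional analyses are named in the same section:

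- Within group: "Differences in the abundance of microbiota species before and after the intervention will be compared using Wilcoxon test".
- Between groups: "Differences in the abundance of microbiota between groups will be compared using Mann-Whitney test".
- Change between groups: "Changes in clinical and multi-omics data before and after the intervention will be compared between groups using analysis of covariance", with the baseline value as covariate.
- Association: "Correlation between abundance of microbiota, metabolite levels, and clinical indicators will be analyzed using Spearman correlation and Partial correlation analysis".

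The Secondary Outcomes section places these data among the ordinary secondary outcomes ("immunologic function, metagenomics, metabolomics, energy expenditure"), with no hierarchy and no formal exploratory status. The Discussion part of the abstract says that the results will "reveal the role of the microbiota-gut-brain axis in exercise-induced metabolic benefits to diabetes". The only primary outcome is "Change in body fat mass measured by bioelectrical impedance analysis". The article gives no number of species, metabolites or correlation pairs.

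**The concern.** This is more than a detail left out of a condensed article. The text fixes a level for all tests and then names high-dimensional analyses that fall under it. A 0.05 level applied feature by feature lets through one in twenty true nulls, however many features are screened. A table of significant species or metabolites would therefore be expected even if no feature in that family differed.

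What is at stake is the mechanistic claim about the gut-brain axis, which draws largely on these screens. Timing also matters. A correction method, or a grouping of features into families, that is chosen after the hits have been seen carries little weight.

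**Working it through.** **1. The plan's own figure.** Sample Size Estimation gives a difference of 1.2 kg, SD 1.9 kg, two-sided α 0.05 and power 80%.

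n per group = 2 × [1.9 × (1.9600 + 0.8416) / 1.2]² = 39.35, rounded up to 40. With 20% loss, 40 / (1 − 0.20) = 50. Both stated figures reproduce. They rest on one primary test at 0.05, so the present point does not touch them.

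**2. Expected false positives.** For m true-null features tested at 0.05, the expected number declared significant is 0.05 × m, whatever the sample size. The values of m are assumptions.

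| Assumed null features | Expected significant |
|---|---|
| 100 | 5 |
| 200 | 10 |
| 500 | 25 |
| 1,000 | 50 |

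For 100 independent null tests, the chance of at least one false positive is 1 − 0.95^100 = 0.994.

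**3. Share of false results among the hits.** With π₀ the proportion of features that are truly null, the approximate share is

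π₀ × 0.05 / [π₀ × 0.05 + (1 − π₀) × power].

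For example, with π₀ = 0.9 and power 0.5: 0.045 / (0.045 + 0.050) = 47%.

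| π₀ | Power 0.3 | Power 0.5 | Power 0.8 |
|---|---|---|---|
| 0.50 | 14% | 9% | 6% |
| 0.80 | 40% | 29% | 20% |
| 0.90 | 60% | 47% | 36% |
| 0.95 | 76% | 66% | 54% |
| 0.99 | 94% | 91% | 86% |

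The share passes one half when π₀ exceeds power / (power + 0.05), which is 0.86, 0.91 and 0.94 for power 0.3, 0.5 and 0.8. The article gives neither π₀ nor the power per feature, so it does not settle where in the range of 6% to 94% this trial would fall.

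**4. What correction would do.** Benjamini-Hochberg at 5%, under independence or positive dependence, holds the expected false share within a family at or below 5%. Bonferroni would hold the family-wise error at 0.05, but with per-feature levels of 0.05 / 200 = 0.00025 or 0.05 / 500 = 0.0001. Take a feature with the standardised effect used for the primary outcome (1.2 / 1.9 = 0.63) and 40 per group. Its power would fall from 81% at 0.05 to 20% or 14%. False discovery control is the more proportionate choice for a screen of this kind.

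**The case against.** The strongest reply is that the sentence fixes a level, not a decision against adjustment. Adjusted p-values or q-values can also be judged at 0.05, and the method may sit in a full protocol or analysis plan that is not shown. That stands in part: the absence of correction is inferred from a rule for all tests together with silence. But nothing in the article signals adjusted values, and its sample size section uses the same 0.05 as an ordinary per-test α.

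The article also has a Discussion heading that calls the gut-brain work an exploration. That is a softer framing, but it is not an outcome label, and it sits beside the stronger promise in the abstract.

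Four stronger readings are tempting and are not supported:

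- **That the omics results will be mostly false.** This needs more than roughly 86% to 94% true nulls at power 0.3 to 0.8. That may be plausible for omics data, but the article does not say it.
- **That thousands of false correlations will appear.** A grid of 200 species by 500 metabolites would give 0.05 × 100,000 = 5,000, but only if every pair is screened and none is related. The article states neither.
- **That every hit would be spurious if exercise had no effect.** Only the between-group comparisons test exercise. All participants receive a diet intervention, so real within-group change is possible without an exercise effect, and microbiota, metabolites and clinical indicators can be truly related in any case.
- **That the clinical secondary outcomes carry an 87% risk of a false positive.** The figure 1 − 0.95^40 = 0.87 treats about 40 outcomes as independent and all null. The list holds strongly overlapping measures, such as weight with body mass index and glucose with HbA1c. Leaving clinical secondary outcomes unadjusted below a single primary outcome is common practice.

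**Conclusion.** The point holds in limited form. The article sets a 0.05 level for all tests and lists species, multi-omics and correlation analyses under it with no stated false discovery control, while attaching a substantive mechanistic claim to them. Read as written, about 5% of the true-null features in each family would be declared significant: 10 to 25 for 200 to 500 null species, and 25 to 50 for 500 to 1,000 null metabolites. These numbers rest on assumed feature counts and on all features being null. The 5% rate itself needs only that each test is valid at its nominal level. Design, primary inference and sample size are untouched, so this is a correction that should be made rather than one on which the trial depends.

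**What to change.** Replace the blanket sentence with a rule in three parts:

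1. The two-sided, unadjusted 0.05 level applies to the primary outcome and the conventional clinical comparisons.
2. Within each omics layer, and within each correlation family (species with clinical, metabolite with clinical, species with metabolite), significance is declared on Benjamini-Hochberg q-values, for example q < 0.05. The families are fixed before the omics data are analysed. Where both covariance analysis and the Mann-Whitney test are run on the same taxa, say which one supplies the p-value or count both in the family.
3. The omics and correlation results are described as exploratory.

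The cost is a few sentences and a routine computing step. The downside is that fewer features will be declared significant. If the full analysis plan already contains such a procedure, it is enough to bring the blanket sentence into line with it.

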### Randomization and Blinding

The randomization digital table is generated using a computer. Participants will be randomly assigned to the exercise or control group in a 1:1 ratio stratified by age and sex. The group assignment will be performed by an independent statistician who would be blinded to the recruitment, intervention, and evaluation of participants. Blinding of participants and researchers (who provide exercise instructions) to group assignment would not be possible due to the specific nature of the study. However, the researchers and statisticians who perform the follow-up assessments and statistical analyses will be blinded to group assignment.

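### Randomisation is stratified by age and sex, but the between-group ANCOVA adjusts only for the baseline value; adding the two factors would be a free, minor improvement

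*Protocol article*

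**What the plan says.** Randomization and Blinding (protocol article): "Participants will be randomly assigned to the exercise or control group in a 1:1 ratio stratified by age and sex".

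Statistical Analysis then names the model for the between-group comparison and its covariate. Changes over the intervention "will be compared between groups using analysis of covariance, with baseline variable levels as covariates". No other covariate is given for that model.

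Age and sex appear in one place in the same section, as a secondary step: "multiple linear regression will be performed for sensitivity analysis of the main clinical variables, adjusting for age, sex, duration of diabetes, and diet".

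Mixed models are also planned, without a list of terms: "Mixed-effect models will be performed to evaluate the effect of exercise intervention on clinical indicators".

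The primary outcome is "Change in body fat mass measured by bioelectrical impedance analysis". Under Sample Size Estimation, "the calculated sample size is 40 for each group to detect a 1.2 kg difference in body fat mass between two groups", with a two-sided 5% level (the sidedness is stated under Statistical Analysis), 80% power and an SD of 1.9 kg. This is raised to 50 per group for 20% loss to follow-up.

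**The concern.** Stratified allocation balances the arms on age and sex, so differences between strata no longer add to the sampling variation of the treatment estimate. A model that leaves the strata out still carries that variation in its residual. Where the factors predict the outcome, the reported standard error then exceeds the true one, the confidence interval is wider than it need be, and the test rejects less often than its nominal level under the null.

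This is a stated choice and not merely detail left to a fuller plan, because the article names the covariate for the between-group ANCOVA and places age and sex elsewhere.

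The sensitivity regression does not fill the gap. It is not the main comparison, it covers only the main clinical variables, and it does not say that it keeps the baseline value. It also adds diet, which is recorded during the intervention (Diet Intervention section) and may itself respond to allocation. No stated model combines the baseline value, age and sex without further terms. What is at stake is some precision in what the trial reports, not the validity of its conclusions.

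**Working it through.** **Inputs from the protocol article.** Difference 1.2 kg, SD 1.9 kg, 80% power, 40 per group before and 50 after allowance for 20% loss (Sample Size Estimation); two-sided 5% level (Statistical Analysis).

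**Assumptions.** R² is the share of the variance in change, after baseline adjustment, that age and sex explain. The documents give no value, so 0 to 0.15 is shown. The 1.9 kg is taken as the SD of change before age and sex are added. The normal approximation is used throughout, with 40 completers per arm.

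**Step 1: the plan's own figure.**

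n = 2 × (1.960 + 0.842)² × 1.9² / 1.2² = 39.35, rounded up to 40 per group; 40 / 0.8 = 50.

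The stated figures reproduce. They come from an unadjusted comparison of two means, so they do not rely on any gain from stratification. Power at 40 per group is 80.6% (normal) or 79.7% (t-test).

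**Step 2: standard errors.**

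- Reported by the baseline-only model: 1.9 × √(2/40) = 0.425 kg.
- True under stratified allocation, and reported by the model that includes the factors: 0.425 × √(1 − R²).

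**Step 3: operating characteristics.**

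- True type I error with factors ignored: 2 × P(Z > 1.96 / √(1 − R²)).
- Power with factors ignored: Φ[(1.2 − 1.96 × 0.425) / true SE]. The threshold stays at 0.833 kg, while the estimate varies less than the model believes.
- Power with factors included: Φ[1.2 / true SE − 1.96].

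| R² | True SE (kg) | Reported SE too large by | Type I error, ignored | Power, ignored | Power, included |
|---|---|---|---|---|---|
| 0 | 0.425 | 0% | 5.0% | 80.6% | 80.6% |
| 0.05 | 0.414 | 2.6% | 4.4% | 81.2% | 82.6% |
| 0.10 | 0.403 | 5.4% | 3.9% | 81.9% | 84.6% |
| 0.15 | 0.392 | 8.5% | 3.4% | 82.6% | 86.5% |

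Worked line for R² = 0.10: √0.90 = 0.949, so the true SE is 0.425 × 0.949 = 0.403. Type I error is 2 × P(Z > 2.066) = 3.9%. Power ignored is Φ(0.911) = 81.9%; power included is Φ(1.017) = 84.6%.

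**Step 4: check by simulation.** This used 80 patients, an assumed two-by-two set of strata with balanced blocks, 8,000 runs per setting, and a deliberately larger R² of 0.20 to make the mechanism visible.

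| Model | Mean reported SE | True SD of estimate | Type I error | Power |
|---|---|---|---|---|
| Baseline only | 0.427 | 0.384 | 3.1% | 81.3% |
| Baseline, age, sex | 0.381 | 0.383 | 5.1% | 86.9% |

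The estimate is equally precise under both models; only the reported uncertainty differs. At R² = 0 both models gave a mean SE of 0.425.

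**The case against.** The strongest reply is that the loss may be nothing. It depends on age and sex predicting change in fat mass after the baseline value is in the model, and no section shows that they do. Sex differences in the level of fat mass are largely carried by baseline already. The sex-specific loads in Table 3 apply only to the exercise arm, and the relative intensity targets are the same for both sexes, so they do not establish that sex predicts change across the trial. This stands: the size of the effect is an assumption.

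It is also fair that the article plans an analysis with age and sex. That lessens the point but does not remove it, for the reasons given above. The mixed-model terms are not listed, and an article may leave them to the full plan, so their absence is not counted as a fault.

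Stronger readings are tempting but unsupported:

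- A reader might infer that the benefit of stratifying is thrown away. It is not: the estimate keeps its precision, and only the reported standard error, interval and p-value fail to reflect it.
- A reader might infer that the trial is underpowered. The sample size never relied on this gain, and baseline-only power stays at about 80% or above.
- A reader might infer that fat mass measured at weeks 4, 8, 12 and 16 gives several chances of success and so inflates false positives. The ANCOVA compares change before and after a 16-week intervention, and the tests at each visit are within-group. No rule says a between-group difference at any visit counts.
- A reader might see a multiplicity problem in "Both the intention-to-treat and full analysis set analyses will be performed". Ranking analysis sets is something an article commonly leaves to the full plan.

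**Conclusion.** The point holds as a minor inefficiency. The article stratifies on two factors and then names a between-group model without them. If those factors explain 5% to 15% of the variance in change, the reported standard error is about 3% to 8% too large and about 1.4 to 3.9 percentage points of power are forgone (82.6 − 81.2 = 1.4; 86.5 − 82.6 = 3.9). If they explain none, there is no effect. The direction is conservative in every case: no bias and no inflation of the type I error.

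The result rests on an assumed R², 40 completers per arm, the planned difference and SD, and allocation that is balanced within strata. Nothing here calls the sample size or the validity of the primary comparison into question.

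**What to change.** In Statistical Analysis, add the randomisation factors age and sex, alongside the baseline value, as covariates in the between-group ANCOVA, and include them in the mixed-effect models. Age can enter as the randomisation stratum or as a continuous variable; the article does not say how age is cut. The sensitivity regression with duration of diabetes and diet can stay as it is.

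The cost is a change of wording and about two degrees of freedom (one for sex; one for age if it is continuous or in two strata). Both variables are already collected at screening and used at randomisation, so no new data, visits or participants are needed. No change to the type of primary model is required to cure this point.

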In the recent decades, the relationship between diabetes and brain health has gradually attracted attention (9–11). Diabetes has been identified as a key risk factor for mild cognitive impairment and dementia (12). Appetite is also altered in patients with obesity and type 2 diabetes. The brain domains of obese people are more sensitive to hunger and have increased activation of reward regions for visual food cues (13). In addition, diabetes is often accompanied by changes in subjective mood states and emotional behavior, such as depression (14, 15). Previous studies have shown that exercise can improve cognitive impairment (16), appetite (17), and depression (18), while most of them have evaluated the brain function using questionnaires and scales. At present, functional magnetic resonance imaging (fMRI) is the mainstay of neuroimaging in cognitive neuroscience, providing a method to investigate the possible causal relationship between brain activity and behavior (19, 20). A recent clinical trial performed in Hong Kong reported that gut microbiota and metabolites mediated exercise-induced metabolic benefits to prediabetic men (21). Exercise affects the gut microbiota composition and microbial metabolites (22), while gut microbiota and their metabolites are involved in regulating behavior and brain activity, including stress response, emotion, pain, feeding behavior, and cognition (23, 24). However, there is a paucity of research elucidating whether the potential physiological benefits of exercise for diabetes mellitus are related to the modulation of the microbiota-gut-brain axis.

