### Data Collection and Follow-Up

Participants will participate in baseline, 4, 8, 12, and 16-week follow-up visits at the Department of Endocrinology and Metabolism, Shanghai Jiao Tong University Affiliated Sixth People’s Hospital. **Table 2** shows the schedule of the study process. The clinical assessments, measurements, and data collection will be conducted by independent researchers who have been trained before the study. Apart from the anthropometry and hematology examination, physicians will also perform a series of clinical assessments, including bioelectrical impedance analysis, MRI of abdomen and lower limbs, magnetic resonance spectroscopy, liver transient elastography, endothelial function ultrasound, flash glucose monitoring, heart rate variability analysis, and exercise-related tests (**Table 2**). The international physical activity questionnaire will be completed to evaluate habitual physical activity over the previous seven days, and a three-dimensional accelerometer tester (wGT3x-BT, Manufacturing Technology Inc, MTI, Florida, America) will be used to continuously monitor the basal physical activity over the following seven days on visit 1, 3, and 5. The dietary habits will be assessed through the three-day food record and food frequency questionnaire. In addition to assessment through conventional questionnaires (e.g., 100-mm visual analog scale, Patient Health Questionnaire-9, Generalized anxiety Disorder scale-7, Problem Areas in Diabetes scale, and Montreal Cognitive Assessment Scale), the brain health of the participants will be accurately evaluated by fMRI. All questionnaires will be filled by participants with the help of trained researchers during a face-to-face interview. Furthermore, blood, urine, stool, and saliva samples will be collected before and after intervention for further multi-omics analysis. Detailed methods of measurements and evaluations are described in the **Supplementary Material**.

**Table 2 T2:** Schedule of the study process.

Time point	Screening	Visit 1	Visit 2	Visit 3	Visit 4	Visit 5
	-2 weeks ~ 0 week	0week	4 weeks	8 weeks	12 weeks	16 weeks
**Eligibility screening**	✓					
**Informed consent**	✓					
**Anthropometrics** (height, weight, body mass index, and waist, hip, and thigh circumference)	✓	✓	✓	✓	✓	✓
**Bioelectrical impedance analysis** (fat mass and percentage, lean mass and percentage)		✓	✓	✓	✓	✓

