### Exploration of the Microbiota-Gut-Brain Axis

Type 2 diabetes mellitus is associated with cognitive decline in all age groups, which affects cognitive domains including memory, information processing speed, attention, and executive functioning (44). Researches have reported that age, education, and co-existence with mild cognitive impairment, depression, and vascular diseases are associated with an increased risk of dementia in diabetes patients (45–47). Exercise can induce benefits to type 2 diabetes related cognitive impairment and dementia (16). Findings from a large, long-term, randomized controlled trial have suggested that a multidomain intervention (diet, exercise, cognitive training, and vascular risk monitoring) can improve or maintain cognitive function in at-risk elderly people (48). Additionally, type 2 diabetes is related with depression and alterations in appetite-related processes (14, 49), both of which can be influenced by exercise training (17, 18, 49). The role of microbiota in regulating gut-brain function contributes to the appreciation of the microbiota-gut-brain axis (23). The gut microbiota produce and release various molecules and metabolites, which in turn mediate the diverse actions of the gut microbiota, including the regulation of energy metabolism, immune system (50), appetite sensation (51), and brain function (52, 53). Evidence from both animal and clinical studies demonstrates that exercise improves intestinal hemostasis by influencing the diversity and composition of the microbiota and metabolite levels (54, 55). However, whether the physiological benefit of exercise in individuals with diabetes is related to the modulation of the microbiota-gut-brain axis is yet to be fully explored.

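### The sensitivity regression adjusts for diet without tying it to a pre-randomisation measure, and its covariate list leaves out the outcome's baseline value

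*Protocol article*

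**What the plan says.** The protocol's Statistical Analysis section plans the main between-group comparison of changes as "compared between groups using analysis of covariance, with baseline variable levels as covariates". Mixed-effect models follow, and then a supporting model: "multiple linear regression will be performed for sensitivity analysis of the main clinical variables, adjusting for age, sex, duration of diabetes, and diet". The section gives neither the diet variable nor its time point. It does not list the outcome's baseline value for this regression, and does not say whether the regressed outcome is the change or the final value.

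Diet is measured in two ways:

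- Data Collection and Follow-Up: "The dietary habits will be assessed through the three-day food record and food frequency questionnaire". Table 2 schedules these questionnaires at Visit 1 (week 0), Visit 3 (week 8) and Visit 5 (week 16).
- Diet Intervention: participants log every meal in an app during the study. Investigators review the log weekly and "upload the dietary record to the data repository for further analysis".

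On whether exercise can alter intake, the Discussion (Exploration of the Microbiota-Gut-Brain Axis) says that "type 2 diabetes is related with depression and alterations in appetite-related processes (14, 49), both of which can be influenced by exercise training". Secondary Outcomes lists "brain health (appetite, mood, and cognitive function"), so appetite is itself an endpoint.

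**The concern.** Age, sex and duration of diabetes at entry cannot be changed by allocation. Diet can, unless it is taken from before randomisation. The only dietary data that the protocol expressly sends to analysis are the on-study app records, and the stated reason for managing diet is to limit its confounding effect during the trial. An analyst could therefore reasonably put on-study intake into the regression.

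That would place a variable on the pathway from exercise to fat mass among the covariates. The coefficient would then answer a different question from the ANCOVA, namely the effect of exercise among people with the same recorded intake. It could also pick up bias from unmeasured causes shared by intake and outcome. A gap between the two analyses might reflect mediation and not fragility, and agreement would not show robustness either. The missing baseline value adds a second difference between the models, which makes any gap harder to interpret.

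**Working it through.** **The plan's own figures.** Inputs from Sample Size Estimation: difference 1.2 kg, SD 1.9 kg, two-sided alpha 0.05, power 80%. n per arm = 2 × (1.960 + 0.842)² × (1.9/1.2)² = 39.4, rounded up to 40. With 20% loss, 40/0.8 = 50 per arm and 100 in total. The sample size reproduces, and this point does not affect it.

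**Effect of adjusting for diet.** Let exercise shift on-study diet by *a* (in SD units), let diet change the outcome by *b* (kg per SD), and let the total effect be −1.2 kg. In a linear model:

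- ANCOVA, or adjustment for pre-randomisation diet, targets −1.2.
- Adjustment for on-study diet targets −1.2 − *ab*.

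The documents give neither *a* nor *b*, so both are assumed over a range. The simulation used 40 per arm, outcome SD about 1.9 kg and 4,000 runs per row. Entries are mean group coefficients in kg.

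| *a* | *b* | −1.2 − *ab* | ANCOVA | Baseline diet | On-study diet |
|---|---|---|---|---|---|
| 0 | 0.6 | −1.20 | −1.21 | −1.21 | −1.21 |
| −0.3 | 0.6 | −1.02 | −1.20 | −1.20 | −1.02 |
| +0.3 | 0.6 | −1.38 | −1.20 | −1.20 | −1.38 |
| −0.5 | 0.6 | −0.90 | −1.21 | −1.21 | −0.91 |
| +0.5 | 0.6 | −1.50 | −1.20 | −1.20 | −1.50 |
| −0.5 | 1.0 | −0.70 | −1.20 | −1.20 | −0.70 |
| +0.5 | 1.0 | −1.70 | −1.20 | −1.19 | −1.70 |

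The non-zero shifts run from 0.3 × 0.6 = 0.18 kg to 0.5 × 1.0 = 0.50 kg. That is 0.18/1.2 = 15% to 0.50/1.2 = 42% of the target, in either direction.

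**Shared cause.** One further setting used *a* = −0.5 and *b* = 0.6, plus an unmeasured factor with a loading of 0.5 on both diet and outcome. On-study adjustment gave −0.77 kg. The shift is 1.20 − 0.77 = 0.43 kg, of which 0.30 kg is mediation and about 0.13 kg is bias from the shared cause.

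**Effect of omitting the baseline value.** In the simulation the group coefficient is about −1.20 kg with or without it, so there is no bias. The standard error without it is larger by the factor 1/√(1 − ρ²), where ρ is the baseline-to-change correlation (not given, so assumed):

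- ρ = 0.2: 1.021, about 2% larger
- ρ = 0.3: 1.048, about 5% larger (simulated SE about 0.41 with baseline, 0.42 without)
- ρ = 0.5: 1.155, about 15% larger

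**The case against.** The strongest reply is that the plan never says the diet covariate is post-randomisation. The other three covariates are baseline characteristics and a week 0 diet record exists, so a baseline reading fits the list at least as well. The sentence about uploading app records does not mention this regression. The document is also a condensed article, and the exact diet variable might be set out elsewhere. All of this stands. A reader might infer that the plan commits to conditioning on on-study intake, but the text only allows it. The point is therefore conditional, and rests on how the stated covariate list is worded rather than on absent detail.

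Two other strong readings also fail. A reader might infer that leaving out the baseline value stops the regression from estimating the randomised effect. It does not: under randomisation the cost is precision and correction of chance imbalance. A reader might also convert a daily intake difference between arms into kilograms of fat and conclude that adjustment could move the estimate by more than the whole 1.2 kg. The documents give no intake difference and no conversion factor. Self-recorded intake is measured with error and would usually adjust only in part. The design also works against a difference, because both arms get the same energy formula, diet chart and weekly review.

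What the reply does not remove is that the wording permits on-study intake, and that the protocol itself supplies the appetite route by which exercise could change it.

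**Conclusion.** The concern holds in conditional form and is minor. If on-study intake is used, the regression estimates exercise at fixed recorded intake and cannot serve as a robustness check of the ANCOVA. The shift is about 0.2 to 0.5 kg against the 1.2 kg target if exercise moves intake by 0.3 to 0.5 SD and intake moves fat mass by 0.6 to 1.0 kg per SD. Those values are assumptions. If the Visit 1 record is used, or exercise does not change intake and no unmeasured cause acts differently by arm, the diet term does no harm. The missing baseline value is purely a loss of efficiency, and its size depends on a correlation that the documents do not give. The ANCOVA carries the baseline covariate and no diet term, so the main comparison and the planned power are untouched.

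**What to change.** Amend the sentence on the sensitivity regression in Statistical Analysis as follows:

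- Define the diet covariate as energy intake from the Visit 1 three-day food record or food frequency questionnaire (name one), completed before allocation is known.
- Add the baseline value of the outcome to the covariates, and state whether the outcome is the change or the final value.
- Report on-study intake by arm descriptively.
- Label any model that includes on-study intake as exploratory or as a mediation analysis, not as a sensitivity analysis.

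The cost is a sentence or two of text. Every variable is already scheduled for collection, and sample size, visits and the ANCOVA stay as they are.
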